### Statistical analysis

2.11

Primary trial analyses will be based on the modified intention to treat (ITT) population in which patients without a measurement of primary outcome will be excluded and additional analyses will also be performed on the per protocol population (PP). Considering that patients who received implantation of implantable cardioverter defibrillator (ICD) or cardiac resynchronization therapy (CRT) within 6 months will be unable to receive the second MRI examination, ITT population will consist of all randomized patients with valid outcome measurement. PP population is a subset of the ITT population in which patients with major protocol deviations will be excluded. Protocol deviations will be defined in the statistical analysis plan.

For the analysis of the primary outcome (change of the indexed LV mass (Δ LVmassi) from baseline to 6‐month follow‐up on CMR), a linear regression model will be employed with treatment as the study variable and baseline measurement of indexed LV mass as a covariate. In addition, adjusted linear model analysis will be performed with the pre‐specified covariates (LVEF, anterior infarction, MVD, presence of MVO on LGE, diabetes, hypertension, and the use of SGLT2i) measured at baseline being added into the above linear model. The crude and adjusted mean differences in the primary outcome together with its 95% confidence intervals at 6‐months will be derived from the linear models. In addition, subgroup analysis of primary endpoint will be performed on the above pre‐specified covariates.

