Analysis of secondary continuous outcomes with single follow‐up measurement will be done in a similar fashion as the primary endpoint analysis. Analysis of secondary continuous outcomes with repeated follow‐up measurement will be performed using a linear mixed model with treatment visit, interaction between treatment and visit as fixed effects, the baseline value of the outcome as covariate if it is available, and subject as random effects. The analysis of binary outcomes will also use a generalized linear/mixed model depending on whether there will be a repeated measurement. Odds ratios with their 95% confidence intervals will be derived from the generalized linear/mixed model analysis. For the analysis of time‐to‐event outcome, Kaplan–Meier curves will be presented and compared by log rank test by treatment group, and hazard ratio and its 95% CI will be calculated using Cox regression model with the treatment arm as the study variable.

Missing primary outcome and secondary outcomes with a single measurement will not be imputed but missing secondary outcomes with repeated measurements will be imputed in sensitivity analysis using the last observation carried forward strategy. Missing baseline covariates will be imputed using simple imputation methods in the covariate adjusted analysis based on the covariate distributions in the sample. For a continuous variable, missing values will be imputed from random values from a normal distribution with mean and SD calculated from the available sample. For a categorical variable, missing values will be imputed from random values from a uniform distribution with probabilities *P*
_
*1*
_, *P*
_
*2*
_,…, and *P*
_
*k*
_ from the sample. Seed for the imputation is set as the date of data analysis (e.g., 270 521).

The study is powered to make a single comparison in the primary outcome at 6 months only and other comparisons are exploratory in nature. Therefore, there is no multiplicity issue. All analyses will be described in detail in the statistical analysis plan. SAS 9.4 will be employed for the statistical analyses.

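### The random imputation in the supplementary covariate-adjusted analysis is seeded by the analysis date, so that adjusted result can shift slightly with the day it is run

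*Protocol article*

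**What the plan says.** Section 2.11 of the protocol article defines the main primary model as a linear regression "with treatment as the study variable and baseline measurement of indexed LV mass as a covariate". A second model is introduced by "In addition, adjusted linear model analysis will be performed with the" and adds seven covariates named in advance: "LVEF, anterior infarction, MVD, presence of MVO on LGE, diabetes, hypertension, and the use of SGLT2i) measured at baseline". Both the crude and the adjusted mean difference are to be reported with 95% confidence intervals.

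On missing data, the same section says: "Missing primary outcome and secondary outcomes with a single measurement will not be imputed". The rule for covariates is: "Missing baseline covariates will be imputed using simple imputation methods in the covariate adjusted analysis based on the covariate distributions in the sample". Continuous covariates are handled in this way: "missing values will be imputed from random values from a normal distribution with mean and SD calculated from the available sample". The rule for categorical covariates reads: "For a categorical variable, missing values will be imputed from random values from a uniform distribution with probabilities", where the probabilities are those seen in the sample. The seed rule comes last: "Seed for the imputation is set as the date of data analysis", with 270 521 given as an example. No pooling over several draws is described, and no analysis date is named.

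**The concern.** A seed is there so that one data set gives one answer. A seed equal to the run date makes a run reproducible afterwards, provided the date is recorded, but it does not settle the result beforehand. If the program is run again on a later day, for instance after a data query, the seed changes, and so do the imputed values, the adjusted difference, its interval and its p value. The wording does not say which date counts when there is more than one run.

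The random draw also brings no benefit here. Treatment is randomised, so a baseline value filled in from pooled data without reference to arm leaves the treatment comparison unbiased, whether it is drawn at random or set to the mean. The draw adds only noise.

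At stake is the stability of a supplementary estimate that will be reported beside the main one, and a small, avoidable choice left to the time of analysis.

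**Working it through.** **Inputs from the article (section 2.10).** Planned difference 4.81 g/m², SD 16.65 g/m², 188 evaluable patients per arm, power at least 80%. The significance level is not stated there; two-sided 5% is assumed from the 95% intervals.

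**Reproducing the plan's figure.** n per arm = 2 × (1.960 + 0.842)² × 16.65² / 4.81² = 188.1, or 189 rounded up, against 188 stated. Power at 188 is 79.98%. The inputs are consistent and are used below.

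**Standard error.** Without covariates: 16.65 × √(2/188) = 1.72. If the covariates explain 10% or 20% of the variance (assumed), it becomes 1.72 × √0.9 = 1.63 or 1.72 × √0.8 = 1.54, so about 1.6.

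**Hand approximation of the between-seed SD.** With a fraction m missing in every covariate and explained variance R², the random draws move the difference in covariate means between arms. This gives roughly

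SD ≈ 16.65 × √R² × (1 − m) × √(2m/188).

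| m | R² | Formula (g/m²) | Simulation, 60 seeds (g/m²) |
|---|---|---|---|
| 0% | 0.1–0.3 | 0 | 0.000 |
| 1% | 0.1 | 0.054 | 0.062 |
| 1% | 0.3 | 0.093 | 0.101 |
| 5% | 0.1 | 0.115 | 0.136 |
| 5% | 0.3 | 0.200 | 0.208 |

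The formula runs a little low because it ignores sampling error in the covariate coefficients.

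**Lower, uneven missingness.** Simulations used n = 376, SD 16.65, R² 0.1–0.2 and 30 seeds per data set. All missing rates are assumptions.

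| Missing | Between-seed SD (g/m²) | Trials whose 5% verdict varies over 30 seeds, at the planned effect |
|---|---|---|
| MVO only, 2–5% | 0.04–0.10 | about 3–4% |
| LVEF 0%, MVO 3%, others 1% | 0.07–0.09 | about 4% |
| LVEF and MVO 5%, others 2% | 0.11–0.15 | 7–10% |

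The percentages are approximate. Simulation error and the assumed strength of each covariate can move them by a point or two.

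**What such a shift does.** At the top of the range, 0.15/1.6 = 0.094 on the z scale. A result at exactly p = 0.05 (z = 1.960) moves to z = 1.866 or 2.054, that is p = 0.062 or 0.040. At the bottom, 0.04/1.6 = 0.025, and p moves to 0.053 or 0.047. As a share of the squared standard error, the seed contributes at most (0.15/1.6)² = 0.9%.

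**Main model.** It contains no imputed term. A patient without baseline LV mass has no change score and is outside the modified ITT set, so nothing is drawn.

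**The case against.** The strongest reply is that this touches only an additional analysis. The main model is free of imputation, and section 2.11 describes comparisons other than the single powered one as exploratory. That stands. A reader might infer that the trial's primary result depends on the calendar; the documents do not support that.

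Second, little should be missing. Every analysed patient has a baseline CMR LV mass, and LVEF comes from the same cine images (sections 2.5 and 2.8), so assuming 5–10% missing LVEF would be implausible. If LVEF by echocardiography is meant, that too is scheduled at baseline (section 2.6). Infarct location and multivessel disease should be known from the ECG and the angiography of the primary PCI. Diabetes and hypertension are routine history, and SGLT2i use is recorded (section 2.4). MVO, which needs usable late-enhancement images, is the realistic gap. This also stands, and it is why the low rates carry the conclusion.

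Third, a reader might infer that someone unblinded could rerun the program until a favourable date turns up. The documents do not say who runs the analysis or whether that person is blinded, and the rule speaks of one date. A single honest run keeps about 5% error. The 30-date figures show how sensitive the result is; they do not predict conduct.

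Finally, the single draw is inferred from the reference to simple imputation and the absence of pooling. The article does not say it outright. The unseen SAP may add detail, but the article itself sets the date rule, so this is a rule fixed badly and not an omission.

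**Conclusion.** The point holds as a minor one. In the covariate-adjusted analysis only, and only if some covariate is missing, the adjusted difference, its interval and, near the threshold, its significance can change with the run date. With about 1–5% missing, mainly MVO, the between-date SD is about 0.04–0.15 g/m² against a standard error of about 1.6, and the 5% verdict varies across 30 dates in roughly 3–10% of simulated trials at the planned effect. These sizes rest on assumed missingness and assumed covariate strength (R² 0.1–0.2), neither of which the documents give. The treatment estimate is not biased by the rule.

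**What to change.** Preferred: replace the random draws by deterministic imputation pooled over arms. Use the observed mean for a continuous covariate, and the observed proportion or a missing category for a categorical one. No seed is then needed, the randomised comparison stays unbiased, and one data set gives one adjusted result.

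Alternative: if random draws are kept, delete the reference to the analysis date and fix one seed number in the SAP before database lock. This removes the dependence on the date but leaves the noise of a single draw.

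Either change takes about two sentences, needs no new data, and has no drawback of substance.

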## RESULTS

3

The study is estimated to be started in November 2021. Recruitment is supposed to be finished by the end of 2022. Primary results of the trial are anticipated in June 2023. The planned end date for the trial is June 2027.

## DISCUSSION

4

The major purpose of PERI‐STEMI trial is to decide whether ARNI could bring superior cardiovascular benefit for patients with STEMI, when it is compared to traditional ACEI treatment. Additionally, through meticulous morphology, function and tissue characterization analysis on CMR, we also aimed to investigate the mechanism of ARNI in improving reverse remodeling, as well as seek CMR indexes for predicting maximum benefit from ARNI among such patients. Potentially, we could provide imaging evidence on application of ARNI in STEMI, and help elucidate the cardiovascular protection mechanism of this medicine.

The most innovative design of this trial is utilization of CMR for the evaluation of ventricular remodeling, cardiac function improvement, and other changes in the comparison between the patients. The promising cardiovascular effects of ARNI for patients with high LV load or who are prone to heart failure have been proven in previous studies. Several animal studies also produce positive evidence on implementation of ARNI in MI.^3^, ^28^ A recent study by Rezq et al demonstrated that compared to ACEI, ARNI is superior in preventing early (at 30 days) adverse clinical events and improving reverse remodeling for patients with STEMI by using echocardiography.^29^ Furthermore, a recent meta‐analysis on LV remodeling studies comparing ARNI versus ACEI/ARB in a heterogenous group of patients reported a distinct improved LV size and hypertrophy for patients prescribed with ARNI, even after short‐term follow‐up (shortest at 3 months in patients with essential hypertension).^22^ Especially, LVmassi presents significant difference in patients with both reduced and preserved LVEF. Nevertheless, CMR study in this scenario is rare. Considering that CMR is recommended as gold standard in cardiac function measurements, our trial sets the CMR‐derived 6‐month remodeling indexes as the primary outcome measurement.^30^, ^31^

Apart from accurate morphological and functional assessment, CMR's incremental prognostic value in predicting long‐term mortality and non‐vital cardiovascular events was also recognized, due to its unique capacity to observe and quantify myocardial fibrosis progression, edema and other tissue characterization change through LGE and mapping sequence.^32^, ^33^ Myocardial stunning is quite commonly seen in patients with STEMI and CMR, especially, and has unique ability to assess myocardial viability by providing accurate quantification of scar burden and myocardium perfusion.^34^, ^35^ Whether ARNI could provide cardiovascular benefits through improving myocardial viability and whether ARNI has a different role in patients with and without myocardium stunning warrant further investigation. A recent study suggested use of CMR for further risk stratification on STEMI patients with lower LVEF on echocardiography.^36^ Thus, with a multiple‐sequence design in our CMR protocol for this trial, we proposed that PERI‐STEMI could better demonstrate the advanced functional benefits ARNI could bring, as well as pave understanding of its cardiovascular mechanism.

Beyond comparing the function on early ventricular remodeling between ARNI and ACEI, another major clinical implication of this study will be that whether ARNI could bring long‐term benefits for patients with STEMI. Another published trial on the use of ARNI in acute MI, namely PARADISE‐MI trial, only included patients with an LVEF ≤40%. And their newly reported results indicated numerical but not statistical difference between ARNI group and ACEI group regarding the pre‐specified primary outcome (https://accscientificsession.acc.org). In addition, the results from PARADISE‐MI trial indicated that long‐term use of ARNI might help improve the outcome. Thus, more evidence is warranted in this field. However, LVEF is only a crude estimate of LV function.^37^ It is not sensitive to myocardial injury, or an ideal predictor for developing adverse LV remodeling.^38^, ^39^ A certain number of patients with normal LVEF developed adverse clinical outcomes while some patients with reduced LVEF at acute phase improved in the long‐term follow‐up.^40^, ^41^ Vaduganathan et al's study provided evidence that an LVEF of 40%–55% might also benefit from several HF treatments, suggesting a potential benefit of ARNI in part of the patients with preserved LVEF, especially for STEMI who are already at high risk of poor prognosis.^42^, ^43^ Thus, it might be inappropriate to arbitrarily only include patients with reduced LVEF when assessing the efficacy of ARNI in STEMI. Considering that no standard cut‐off for other CMR indexes has been set up to decide the patients at stake, our trial is designed not to exclude patients only based on imaging markers immediately after PPCI. Hopefully, this could contribute by answering the question whether additional CMR indexes could be used for further risk stratification of the patients with STEMI.

Another merit of this trial is that we rigorously include patients with timely revascularization, and who are hemodynamically stable. Considering the potential effects PPCI procedure might have on the baseline myocardium characterization of the patients, inclusion criteria is enriched to avoid the bias from procedure or the baseline condition of the patients. In addition, for these patients, possibility of having a CRT is relatively low, and thus a later exclusion could be prevented.

### Limitations

4.1

As with any other clinical trial, our study has several limitations that should be mentioned. First, only hemodynamic stable patients who receive successful revascularization within 12 h, and who do not receive CRT or ICD implantation within 6 months will be finally included, thus certain bias exists and the interpretation of our results should be careful. Second, there might be a regional variation in the clinical outcomes in this multi‐center study. The study is powered to assess the difference in the change of the indexed LV mass (Δ LVmassi) from baseline to 6‐month follow‐up on CMR, which is a surrogate endpoint. We expect to collect some data on clinical outcomes from this study to plan a future large randomized clinical trial to assess the clinical efficacy of ARNI. Third, the major index observed in this study is an imaging marker, which will be measured objectively through an independent and blinded Core Laboratory. However, bias might still exist because the patients are not blinded. Nevertheless, LV remodeling is a relatively objective change and has not been reported related to the patient's subjective feeling. Measurements of primary and secondary outcomes including both imaging reading and clinical events assessment, data management and development of statistical analysis plan will be kept rigorously blinded to avoid potential bias. Finally, as this is an MRI study and intended to compare the effects of ARNI versus ACEI on LV remodeling, the results of the study will need to be carefully interpreted when transferring to clinical application. Although clinical outcomes will also be assessed in our study, those analyses will be exploratory in nature as the study is not powered to assess the effects of ARNI on clinical outcomes.

## CONCLUSION

5

Patients with STEMI are prone to heart failure and adverse ventricular remodeling is a risk factor at early follow‐up. The PERI‐STEMI trial will be the first CMR study to test the effects of ARNI in patients with STEMI. Results of this trial will provide evidence on implementation of ARNI therapy in STEMI, and help elucidate the cardiovascular protection mechanism of ARNI.

## Data Availability

Data sharing not applicable to this article as no datasets were generated or analysed during the current study.
